### 8.1.3 *Analysis Populations*

Two different sets of patients will be defined to perform analyses. A “Full Analysis Set” (FAS) following the principle of intent-to-treat (ITT) will include every patient as randomized and compare the patients according to the group to which they were randomly allocated, regardless of patients' compliance, or withdrawal from the study. It is the most cautious approach and so minimizes type 1 error, helps preserve prognostic balance in the study arms and allows for the greatest generalizability.

Secondly, an analysis of all per protocol treated patients will be performed. The “Per Protocol Set” (PPS) is a subset of the FAS patients who are compliant with the study protocol. The PPS sample will consist of all subjects from the FAS group without any major protocol violation.

First and foremost, confirmatory analyses on primary efficacy variable will be performed on the FAS patients but a secondary analysis will also be performed based upon the Per Protocol Set, to assess the sensitivity of the analysis to the choice of analysis population. The ITT analysis will be considered as the primary one.

Patients who received the cellular product or Placebo but dropped-out post-hoc because of cell count insufficiency will be evaluated separately.

The safety population will comprise all patients randomized into the study, in which each patient's treatment is as taken on the study. Safety evaluations will be performed on the safety population.

## 8.2 **General Considerations**

In statistical analyses no missing values will be replaced.

All statistical analyses are performed by the Institute of Medical Informatics and Biometry of the University of Rostock. Statistical analyses will be carried out using the SPSS statistical analysis system, version 14.0.

All statistical tests will be conducted using a two-sided test with  $\alpha=0.05$ , unless otherwise stated.

For all data collected during the trial and reported in the CRF describing the sample, listings of the individual raw data as well as tables of sample characteristics and/or frequencies will first be given. Continuous data will be summarized first by treatment group, secondly by certain study time points, thirdly by each study center using descriptive statistics (mean, median, standard deviation [SD], minimum and maximum, number of available observations and number of missing observations). It will be done for absolute and percent changes and if appropriate from baseline screening too.

Categorical data will be summarized first by treatment group, secondly by certain study time points, thirdly by each study centers. The numbers and percentages of each of categories, the number of available observations and the number of missing observations will be presented in frequency tables.

Any outliers that are detected during the blind review of the data will be investigated. Methods for dealing with outliers will be defined in the SAP or in an addendum to the SAP, prior to unblinding.

The statistical analysis of study results will be performed according to the CPMP guidelines for “Biostatistical methodology in clinical trials in applications for marketing authorizations for medicinal products” and the ICH guideline “Statistical principles for clinical trials”.

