### **3.2 Endpoints**

#### Primary endpoint

The primary endpoint is LVEF at 6 months postoperatively, measured by MRI at rest. Cardiac MRI is established as the gold standard for determination of LV function (LVEF and LV volumes).

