### 4.3 Patient Withdrawal and Replacement

Patients may withdraw from the study at any time without penalty and for any reason without prejudice to his or her future medical care. All patients will be closely monitored by their individual cardiologist and general practitioner and treated as appropriate, according to the guidelines issued by the national and international cardiology organizations that relate to patients with coronary artery disease and patients with congestive heart failure. The Investigators reserve the right to conduct additional follow-up examinations.

Patients must be withdrawn under the following circumstances:

- The patient withdraws consent;
- Pregnancy. If patients are to withdraw due to pregnancy, they should be followed-up until the outcome for the mother and fetus are known.
- If serious clinical events (e.g., emergency surgery, myocardial infarction, stroke, fever  $\geq 38.5^{\circ}\text{C}$ ) occur between recruitment and planned surgery.

Patients may be required to withdraw after discussion with the Sponsor and/or Investigator for the following reasons:

- Adverse event(s);
- At the discretion of the Investigator;
- Violation of eligibility criteria;
- Deviation from the treatment plan specified in the protocol (e.g., incorrect administration of the study drug, failure to attend study visits).

In all cases, the reason(s) for withdrawal, and the primary reason, will be recorded on the case report form (CRF). If a patient is prematurely withdrawn from the study for any reason, the Investigator will make every effort to perform the evaluations described for the Early Termination Visit (see Section 7.2.6.2).

An excessive withdrawal of patients can render the study uninterpretable. Therefore unnecessary withdrawal of patients should be avoided. In case of withdrawal, all efforts should be made to complete and report the observation and justification of withdrawal in as much detail as possible. Withdrawn patients that dropped-out of the study because of SAE will not be replaced. However, patients who are not able to reach the primary endpoint because of their body size/weight may be replaced.

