#### 6.1.1 *Left Ventricular Ejection Fraction (LVEF)*

LVEF will be measured by cardiac MRI, established as the gold standard for determination of LV function (LVEF and LV volumes). According to the schedule cardiac MRI will be performed at Assessment I, Assessment III and Assessment V.

LVEF at 6 months postoperatively (Assessment V), measured by MRI at rest is the *primary endpoint*.

*Secondary endpoints* include change in LVEF pre-operatively (Assessment I) with 6 months post-operatively (Assessment V). This will be assessed by cardiac MRI scans and echocardiography (see Section 6.1.5).

Cardiac MRI scans will be performed in accordance with the Schedule of Assessments (see Table 2). The analysis and interpretation of data from the cardiac MRI scans concerning LV function parameters will be done centrally by a reviewer blinded to the treatment the patient has received.

LVEDD, LVEDV, LVESD and LVEF will be recorded in the CRF. The main area of impaired LV infarction will also be recorded in the CRF and quality will be recorded as normal, akinetic, hypokinetic or dyskinetic.

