**Figure 7: Left ventricular segmentation**

#### 6.1.6 *Echocardiography*

Echocardiography will be performed as additional parameter to MRI in accordance with the Schedule of Assessments (Table 2, Assessments I, III, V, VI: Screening, Hospital Discharge, 6-Month Follow-Up (FU), 24-Month FU). The analysis and interpretation of data from the echocardiography concerning LV function parameters will be done centrally by a reviewer blinded to the treatment the patient has received. The date of performance will be recorded in the CRF. The heart rate (per min) and the quality of the images will be documented: good, middle, bad, orthograde ultrasound not measurable. LVEDD (mm), LVEDV (cm^3), LVESD (mm), LVEF (%; four chamber view), IVSD (mm), LVPWD (mm) and LVOT (mm) will be recorded in the CRF. The main area of impaired LV infarction will be recorded in the CRF. Quality assessment of wall movement will be recorded as normal, akinetic, hypokinetic or dyskinetic and the presence of an aneurysma. Pericardial effusion will be assessed: no/yes, if yes: document size (mm) and location (anterior, posterior, lateral, circular).

Furthermore the following has to be documented:

- Mitral regurgitation (none, mild, moderate)
- Tricuspid regurgitation (none, mild, moderate; if mild or moderate:  $\Delta$  Pmax in mm/Hg)
- Transmittal flow: VE in cm/sec, VA in cm/sec, VE/VA < 1 or > 1; DT (VE) in msec), VTI (LVOT) in cm
- Aortic valve regurgitation (none, mild, moderate), RVEDD (RVOT) in mm, LA (left atrium) in mm, RA (right atrium, 4 CV) in mm
- Unwanted tissue changes; no/yes; if yes, describe

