### **8.5 Efficacy Analyses**

The trial will be conducted in seven study sites. Therefore centers will be considered as possible prognostic factor influencing the outcome.

With regard to possible baseline and study site effects, the two-sided hypothesis for the continuous primary efficacy variable LVEF at 6 months postoperatively (comp. section 6.1.1) will be assessed using analysis of covariance (ANCOVA) adjusting for baseline LVEF and study sites.

Secondary efficacy variables (comp. section 6.1.1) will be analyzed in a strictly explorative way. The distance walked pre-op and post-op will be compared. If p-values are computed, no adjustment for multiple testing will be made and they will be interpreted in the exploratory sense. Similarly, confidence intervals computed will be interpreted as interval estimates for presence or absence of effects in the study data.

In order to check differences between the treatment groups for the fifth secondary endpoint (death, myocardial infarction, need of reintervention) an unadjusted survival analysis with Kaplan-Meier estimations will be performed using the logrank test.

Details of the statistical analyses will be documented in SAP (Statistical Analysis Plan) that is to finalize before unblinding.

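### With no replacement of missing values and a single-timepoint ANCOVA, the confirmatory full-analysis-set test becomes a completer analysis, which does not match its definition as all patients randomised

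*Protocol*

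**What the plan says.** Protocol 8.2 sets the missing-data rule without exception: "In statistical analyses no missing values will be replaced". The same section defers outlier handling to the SAP, but not this rule.

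Protocol 8.1.3 says of the full analysis set (FAS) that it "will include every patient as randomized and compare the patients according to the group to which they were randomly allocated", irrespective of compliance or withdrawal, and that "First and foremost, confirmatory analyses on primary efficacy variable will be performed on the FAS patients". The endpoint is fixed in 3.2: "The primary endpoint is LVEF at 6 months postoperatively, measured by MRI at rest". Under 8.5 the hypothesis "will be assessed using analysis of covariance (ANCOVA) adjusting for baseline LVEF and study sites".

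Further LVEF data are planned. Section 6.1.1 states: "According to the schedule cardiac MRI will be performed at Assessment I, Assessment III and Assessment V". Section 6.1.6 adds: "Echocardiography will be performed as additional parameter to MRI in accordance with the Schedule of Assessments"; echo is centrally read and includes LVEF at screening, discharge and 6 months. These values serve secondary endpoint 1.

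Section 8.1.2 lists a missing 6-month LVEF as a reason for exclusion from the per-protocol set (PPS) only. Section 4.3 deals with one cause of a missing scan by recruitment: "patients who are not able to reach the primary endpoint because of their body size/weight may be replaced".

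**The concern.** Each statement is ordinary on its own. Together they conflict. The FAS is meant to keep a patient without a 6-month MRI, since only the PPS excludes such a patient. With one outcome time and no replacement, the model drops that patient anyway. The confirmatory result then rests on completers while being described as intention-to-treat, and the PPS cannot show whether the loss matters because it omits the same people.

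The protocol's own routes to a missing scan are largely post-operative: death, withdrawal after adverse events (4.3), and withdrawal after unblinding (5.4). Baseline LVEF and site may not capture these. At stake is bias in the primary contrast if such loss is related to early post-operative LVEF and falls unequally on the arms.

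**Working it through.** **1. The plan's own figures (8.7).** Inputs: difference 4.5, SD 7.5, two-sided 5%, 90% power, 15% drop-out.
- A two-sample t-test with the noncentral t distribution at 60 per group gives power 90.3%, so 60 is confirmed.
- 60 / (1 − 0.15) = 70.6, rounded up to 71 per group, or 142. Confirmed.
- Non-evaluable patients allowed for: 142 − 2 × 60 = 22.
- Power with 71 per arm by share missing: 0%, 94.4%; 15%, 90.5%; 20%, 88.7%; 25%, 86.6%.

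The planned loss is already paid for.

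**2. Bias by arithmetic.** If missing patients have a true mean lower than completers by g in an arm with missing share m, the completer mean is too high by m × g. The contrast (cells minus placebo) is off by m_cells × g_cells − m_placebo × g_placebo. The protocol gives none of these gaps; the range is assumed.
- 15% in both arms, equal gap: 0.
- 20% versus 10%, gap 3 to 10 points: (0.20 − 0.10) × 3 = 0.3 to (0.20 − 0.10) × 10 = 1.0. The sign reverses for 10% versus 20%.
- 15% in both arms, gap 7.5 in one arm only: 0.15 × 7.5 = 1.1.

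**3. Bias by simulation.** This allows for baseline adjustment. Assumed: 71 per arm; SD 7.5; logistic missingness, more likely with low discharge LVEF; no treatment effect at discharge; site omitted; 3,000 runs. Correlations (baseline–discharge, baseline–6 months, discharge–6 months) are set A (0.6, 0.5, 0.6) and set B (0.7, 0.6, 0.8).

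| Missing, cells / placebo | True difference | Completer ANCOVA, A; B | Estimate also using discharge LVEF, A; B |
|---|---|---|---|
| 15% / 15% | 0 | 0.00; 0.00 | −0.01; 0.00 |
| 10% / 20% | 0 | −0.28; −0.32 | −0.03; 0.01 |
| 5% / 25% | 0 | −0.49; −0.62 | 0.02; 0.03 |
| 20% / 10% | 4.5 | 4.77; 4.87 | 4.52; 4.55 |

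In the last row the same runs without any missing data gave 4.52 and 4.55, so the loss accounts for 4.77 − 4.52 = 0.25 and 4.87 − 4.55 = 0.32. A separate simulation with the same kind of mechanism gave 0.24 at 20% versus 10%, and 0.14 at 18% versus 12%. Completer type I error was 5.2–5.4% at 15%/15% and 7–9% at 5%/25%, which is an extreme split.

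**4. Scale.** The standard error at 60 per arm is 7.5 × √(2/60) = 1.37. A bias of 0.14 to 0.32 is 0.10 to 0.23 standard errors, or 3% to 7% of 4.5.

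**5. Precision.** The completer variance factor is 1 / 0.85 = 1.176, so the effective size is 142 / 1.176 = 121. If auxiliaries explain a share R² of residual variance and are available for a share q of missing patients, the factor is 1 + 0.176 × (1 − q × R²). For R² of 0.3 to 0.7 (assumed), q = 1 gives 126 to 135; q = 0.5 gives 124 to 127.

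**The case against.** The strongest reply is that the effect is small and conditional. Treatment is double-blind and given once during the same operation, and nothing in the protocol predicts unequal loss. With loss driven by discharge LVEF but equal in both arms, the contrast is unbiased. That stands: a reader might infer that completer ANCOVA fails whenever loss depends on post-operative function, but the simulation does not support this.

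Other stronger readings also fail:
- *The trial is underpowered.* It is not; the drop-out allowance covers completers.
- *22 patients will lack the endpoint.* The 15% is an overall drop-out rate. By 3.3 it includes patients with low cell yield, and those between 0.1 and 0.5 × 10⁶ cells are still followed. The figure of 22 is an upper bound under the plan's assumption.
- *Effective size would rise to 126–135.* That needs auxiliaries for every missing patient. The 6-month echo belongs to the same visit as the MRI, and early deaths and patients not followed after a very low yield have no discharge scan.
- *Data are discarded and deaths vanish.* Discharge MRI and echo feed a secondary endpoint, death is in the log-rank analysis (8.5), and missing counts are tabulated (8.2).
- *FAS and PPS are nearly the same.* The PPS also removes eligibility and other major violations. Only the missing-LVEF exclusion is shown to be shared.

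It can also be said that a likelihood model replaces no values, so 8.2 alone does not forbid it. True, but 8.5 fixes the single-timepoint ANCOVA, and an SAP that imputed would contradict 8.2. The conflict therefore sits in the protocol and cannot be left to the SAP.

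**Conclusion.** The point holds in a limited form. Sections 8.2 and 8.5 turn the confirmatory FAS test into a completer analysis, contrary to 8.1.3, and the one sensitivity population named cannot test the consequence. No stated sample size or power is wrong.

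Bias in the contrast needs missingness that depends on post-operative LVEF and also differs by arm, in rate or in kind. It is then roughly 0.1 to 0.3 points for 18% versus 12% up to 20% versus 10% loss, and about zero for equal loss of the same kind. These sizes rest on assumed correlations, missingness strength and arm-specific rates, none of which the protocol gives. The larger values in the working need a 5%/25% split or an assumed gap not reduced by baseline adjustment. Any precision gain is modest. This is an inexpensive improvement worth making before unblinding, not a defect that invalidates the design.

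**What to change.** For the primary endpoint, replace the 8.2 sentence and align 8.5 with it:

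- Analyse all FAS patients with a likelihood-based repeated-measures model on MRI LVEF, with baseline as covariate, discharge and month 6 as outcomes, site, and arm by visit. The alternative is multiple imputation using discharge MRI and any available echo LVEF.
- Keep completer ANCOVA as a sensitivity analysis, with a missing-not-at-random analysis detailed in the SAP.
- State how deaths before 6 months enter the endpoint, since neither method should assign them an LVEF by default, and report deaths by arm beside the result.
- State whether an MRI from the early-termination visit (7.2.6.2) counts as the 6-month value.
- In 8.8, take the stage-wise p-values p₁ and p₂ from this same model rather than from a t-test.

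The cost is protocol and SAP wording and some analysis work; no new data are needed. The downside is a missing-at-random assumption, which the sensitivity analyses examine. Discharge data cannot help patients lost before discharge.

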### **8.3 Demographics, Baseline Characteristics and Concomitant Medications**

Demographic data, medical history, concomitant disease and concomitant medication will be documented and analyzed. All data will be summarized by means of descriptive statistics (mean, SD, median, minimum, maximum, number of available observations and number of missing observations) or frequency tables, stratified by treatment.

For all data collected during the procedure, listings of the individual raw data as well as tables of sample characteristics and/or frequencies will be given. Graphic presentations will be produced.

### **8.4 Treatment and Study Compliance**

Treatment will be administered by study personnel hence patient compliance with study treatment will not be monitored (comp. Section 5.6) and analyzed.

Patients that are not attendant at study visits or refuse to undergo certain assessments are non-compliant with the study protocol. Listings and frequency tables of those patients are provided.

### **8.5 Efficacy Analyses**

The trial will be conducted in seven study sites. Therefore centers will be considered as possible prognostic factor influencing the outcome.

With regard to possible baseline and study site effects, the two-sided hypothesis for the continuous primary efficacy variable LVEF at 6 months postoperatively (comp. section 6.1.1) will be assessed using analysis of covariance (ANCOVA) adjusting for baseline LVEF and study sites.

Secondary efficacy variables (comp. section 6.1.1) will be analyzed in a strictly explorative way. The distance walked pre-op and post-op will be compared. If p-values are computed, no adjustment for multiple testing will be made and they will be interpreted in the exploratory sense. Similarly, confidence intervals computed will be interpreted as interval estimates for presence or absence of effects in the study data.

In order to check differences between the treatment groups for the fifth secondary endpoint (death, myocardial infarction, need of reintervention) an unadjusted survival analysis with Kaplan-Meier estimations will be performed using the logrank test.

Details of the statistical analyses will be documented in SAP (Statistical Analysis Plan) that is to finalize before unblinding.

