#### Statistical Methods

The statistical analysis of study results will be performed according to the CPMP guidelines for “Biostatistical methodology in clinical trials in applications for marketing authorizations for medicinal products” and the ICH guideline “Statistical principles for clinical trials”.

For all data collected during the trial and reported in the case report forms describing the sample, listings of the individual raw data as well as tables of sample characteristics and/or frequencies will first be given. Continuous data will be summarized first by treatment group, secondly by certain study time points, thirdly by each study centers using descriptive statistics (mean, median, standard deviation [SD], minimum and maximum, number of available observations and number of missing observations). It will be done for absolute and percent changes from baseline too.

Categorical data will be summarized first by treatment group, secondly by certain study time points, thirdly by each study centers. The numbers and percentages of each of categories, the number of available observations and the number of missing observations will be presented in frequency tables.

The trial will be conducted at seven study sites. Therefore centers will be considered as possible prognostic factor influencing the outcome.

With regard to possible baseline and study site effects, the two-sided hypothesis for the continuous primary efficacy variable LVEF at 6 months postoperatively (comp. section 6.1.1) will be assessed using analysis of covariance (ANOVA) at adjusting for baseline LVEF and study site at a 5% level of significance.

Secondary efficacy variables (comp. section 6.1., 6.2.) will be analyzed in a strictly explorative way. If p-values are computed, no adjustment for multiple testing will be made and they will be interpreted in the exploratory sense. Similarly, confidence intervals will be computed. In order to check differences between the treatment groups for the fifth secondary endpoint (death, myocardial infarction, need for reintervention) an unadjusted survival analysis with Kaplan-Meier-estimations will be performed using the log rank test.

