## **1.2 Rationale**

Stem cell therapy for myocardial regeneration after myocardial infarction is an exciting new field of medical research that has the potential to revolutionize cardiovascular medicine. Despite significant improvements in emergency treatment, myocardial infarction leads to a net loss of contractile tissue in many patients with coronary artery disease. Often, this is the beginning of a downward spiral towards congestive heart failure and life-threatening arrhythmia. Other than heart transplantation with its obvious limitations, current therapeutic means aim at preventing further episodes of myocardial ischemia and at enabling the organism to survive with a heart that is working only at a fraction of its original capacity. Those are far from representing a cure. In this situation, it is understandable that cardiac stem cell therapy attracts considerable attention and raises many hopes. In order to adequately judge both the potential benefits and the limitations of cardiac cell therapy, more understanding of the mechanism and the consequences of myocardial infarction and its current treatment concepts is needed.

The myocardium consists of terminally differentiated cells without a clinically relevant potential for regeneration. Hence, cardiomyocytes that were subject to necrotic or apoptotic cell death in acute myocardial infarction, ischemic cardiomyopathy, or myocarditis cannot be replaced by new contractile cells. Instead, remodeling processes ultimately lead to interstitial myocardial fibrosis or formation of a transmural fibrotic scar that further impairs systolic and diastolic ventricular function and may progress into formation of a LV aneurysm. Surgical or interventional revascularization of ischemic myocardium effectively treats angina, prevents myocardial infarction, improves function of still viable myocardium, and pharmacological therapy appears to have a beneficial impact on remodeling processes. However, viability and function of necrotic myocardium cannot be restored with current therapeutic options. Recently, transplantation of cells into infarcted myocardium has evolved a means to ultimately achieve this goal (Leri et al 2005, [name] 2006). As most of ischemic heart diseases

result in chronic heart failure (Gheorghiade and Bonow, 1998) there is a high medical need for new regenerative therapies.

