### 6.1.5 *Cardiac MRI Scan*

Cardiac MRI Scan will be performed in accordance with the Schedule of Assessments (Table 2, Assessments Screening, Hospital Discharge, 6-Month Follow-Up). The analysis and interpretation of data from the cardio MRI concerning LV function parameters will

be performed centrally by a reviewer blinded to the treatment the patient has received. The value for LVEF for Assessment I/Screening will be determined within 12 hours by the MRI Core Lab personnel and the result will be forwarded immediately to the treating physician. The following will be recorded continuously in the CRF:

- Date of recording
- LV mass ( $\text{g/m}^2$ ), body surface ( $\text{m}^2$ ), weight (kg), height (cm)
- LVEDV, LVESV, LVEF (%), Scar tissue total (g), Non-viable tissue (g)
- Ventricle function and wall motion (quality) for segments 1-17 (see Figure 7; 1 = hyperkinetic, 0 = normokinetic, -1 = hypokinetic, -2 = akinetic, -3 = dyskinetic)
  - Wall motion thickening (%)
  - Regional muscle mass (g)
- Perfusion at stress and at rest for segments 1-17 (see Figure 7; 0 = normal, 1 = reduced subendocardial, 2 = reduced transmural)
- Vitality/late enhancement (LE) for segments 1-17 (see Figure 7); LE volume (% LV mass), transmural LE (%)
- Total assessment vitality for segments 1-17 (see Figure 7; 0 = normal, -1 = stunned, -2 = hibernating, -3 = infarct)
- Unwanted tissue changes; no/yes, if yes, describe
- Pericardial effusion (no, few, moderate, much)
- Pleural effusion (no, few, moderate, much)
- Thrombus no/yes

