## 8.7 Determination of Sample Size

Considerations for determining the sample size of the primary efficacy parameter LVEF at 6 months postoperatively, measured by MRI at rest, were carried out on the basis of the results of a previous efficacy pilot trial with  $n=20$  patients per group conducted in Rostock by [name] and co-workers (Stamm et al, 2007). For LVEF at 6 months postoperatively the results were  $47.1 \pm 7$  for patients of the CABG & cell injection group and  $41.3 \pm 8$  for patients of the CABG only group.

The stratification of the primary analysis by center is neglected in the sample size calculation. Instead of the analysis of covariance (ANCOVA) to be used in the primary analysis, the two-sample  $t$  test scenario with equal variances is considered.

Sample size determination is done under the assumption of a two-sided type I error ( $\alpha$ ) at 5% and a type II error ( $\beta$ ) at 10% (i.e. a power at 90%). Since there is some uncertainty regarding the expected means and standard deviations Table 3 presents how many patients per group are necessary for several scenarios, e.g. to show a difference of 3.5 to 5.5 between the two groups.

The scenario of a difference of about 4 to 5 is considered as a clinical relevant difference. With a difference of 4.5 and a standard deviation of 7.5, at least  $n=60$  patients per group are necessary and with an additional 15% drop-out rate a total of at least 142 patients will be randomized.

For  $n=60$  patients per group, Table 4 presents the power for some other scenarios of mean and standard deviation.

Sample size calculation was done using the commercial program nQuery Advisor 5.0, section 8, table MTT0-1 [Elashoff, 2002]. Computation was realized using central and non-central  $t$ -distribution where the non-centrality parameter is  $\sqrt{n} \delta / \sqrt{2}$  and  $\delta$  is defined as effect size  $|\mu_1 - \mu_2| / \sigma$  [O'Brien RG, Muller KE, 1993].

**Table 3: Number of Patients Necessary to Show Differences of the Primary Efficacy Parameter LVEF at 6 Months Postoperatively (Two-Sided,  $\alpha = 0.05$ ,  $1 - \beta = 0.90$ )**

| LVEF 6 months postoperatively
Difference of means between CABG & cell injection group
and CABG only group (standard deviation within both
groups) | Number of patients per
group |

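### The primary ANCOVA is valid, but it leaves out screening MRI non-viable tissue, a plausible prognostic covariate already collected, so some precision may be forgone

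*Protocol*

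**What the plan says.** Section 8.5 fixes the primary model: 6-month LVEF "will be assessed using analysis of covariance (ANCOVA) adjusting for baseline LVEF and study sites". The synopsis repeats it, "adjusting for baseline LVEF and study site at a 5% level of significance". Neither names another covariate.

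Section 6.1.5 lists what is recorded from each cardiac MRI, including "LVEDV, LVESV, LVEF (%), Scar tissue total (g), Non-viable tissue (g" (the last two in grams), together with segmental late enhancement and viability. The scans are at "Table 2, Assessments Screening, Hospital Discharge, 6-Month Follow-Up". By section 4.5, randomization follows completion of screening, so the screening scan precedes it.

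Section 1.2 says that revascularization "improves function of still viable myocardium", whereas "viability and function of necrotic myocardium cannot be restored with current therapeutic options". Every patient undergoes CABG (section 5.10).

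Section 8.7 sizes the trial with a two-sample t test in place of the ANCOVA and takes no credit for any covariate. Section 8.2 states that missing values are not replaced. Section 8.8 takes the p-values of both stages from a t-test.

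**The concern.** Two patients can have the same screening LVEF for different reasons: in one the poorly contracting wall is mostly viable, in the other mostly scar. On the protocol's own rationale, grafting should help the first more, in either arm. The entry criteria admit akinetic, hypokinetic or hypoperfused areas (section 4.1), so both kinds of patient can enrol. Baseline LVEF alone does not separate them, whereas the screening MRI may.

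If non-viable tissue predicts 6-month LVEF beyond baseline LVEF and site, that variation stays in the error term of the primary comparison. The confidence interval is then wider, and power lower, than the collected data would allow.

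**Working it through.** **1. The protocol's own figure.** From section 8.7: "Sample size determination is done under the assumption of a two-sided type I error" of 5%, with 90% power. "With a difference of 4.5 and a standard deviation of 7.5, at least" 60 patients per group are needed. The non-centrality parameter is √(n/2) × difference/SD = √30 × 4.5/7.5 = 3.29. With 118 degrees of freedom the power is 90.3%. Allowing for 15% drop-out, 60/0.85 = 70.6, so 71 per group and 142 in total. The stated figures reproduce.

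**2. Effect of one more covariate on the standard error.** Let r be the partial correlation of screening non-viable tissue with 6-month LVEF, given baseline LVEF and site. The residual SD, and with it the standard error of the treatment effect, is multiplied by √(1 − r²). The protocol gives no r, so the values below are assumptions.

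**3. Effect on power at a difference of 4.5, 60 per group.** The planned ANCOVA uses 7 degrees of freedom for baseline LVEF and seven sites (111 left); the extra covariate uses one more (110 left). Two readings of the SD are shown.

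- Reading A: 7.5 is already the residual SD of the planned ANCOVA.
- Reading B: 7.5 is the marginal SD, and baseline LVEF correlates 0.65 with 6-month LVEF. The planned residual SD is then 7.5 × √(1 − 0.65²) = 5.70.

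| r (assumed) | SE reduction | Power, reading A | Power, reading B |
|---|---|---|---|
| 0 | 0% | 90.3% | 99.0% |
| 0.1 | 0.5% | 90.6% | 99.1% |
| 0.2 | 2.0% | 91.4% | 99.2% |
| 0.3 | 4.6% | 92.7% | 99.4% |
| 0.4 | 8.3% | 94.5% | 99.7% |
| 0.5 | 13.4% | 96.4% | 99.9% |

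As an intermediate case, if baseline LVEF correlates 0.5 with the outcome (assumption), the planned ANCOVA has 96.4% power, and r = 0.2 to 0.5 gives 97.0% to 99.1%.

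At a difference of 3.5, which is in Table 4, there is more room for a gain. Reading A goes from 71.7% to 73.4% (r = 0.2) or 83.3% (r = 0.5). Reading B goes from 91.5% to 92.6% or 97.1%.

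**4. Which reading fits better.** Section 8.7 takes its SDs from the raw 6-month values of the pilot trial (7 and 8) and uses a t test, so 7.5 looks like a marginal SD. The pilot also bears on the baseline correlation. Section 1.1.2.5 gives mean changes of +9.7 and +3.4, a difference of 6.3, with p = 0.0009 in the text and 0.009 in the legend of Figure 3. Assume a t-test with 20 per group:

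- p = 0.0009: t = 3.60, SE = 6.3/3.60 = 1.75, SD of change = 1.75 × √10 = 5.5.
- p = 0.009: t = 2.75, SE = 2.29, SD of change = 7.2.

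The baseline and 6-month SDs in that section are 8 and 8 (cells) and 10 and 8 (control). The average variance of change is [(64 + 64) + (100 + 64)]/2 − ρ(64 + 80) = 146 − 144ρ. Setting this equal to 5.5² or 7.2² gives ρ of about 0.80 or 0.65. This is rough: the data are echocardiographic, the test is not named, and the two p-values disagree.

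**5. Missing baseline values.** With no replacement (section 8.2), a patient without the covariate drops out of the model. The gain is cancelled once a fraction of about r² of patients lack it: 4% at r = 0.2, 9% at 0.3, 16% at 0.4.

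**The case against.** The strongest objection is that nothing here is wrong. Baseline outcome plus the randomization stratum is a standard, coherent model, and one more useful covariate could be proposed for almost any trial. Section 1.2 is general background; it does not say that MRI non-viable mass predicts 6-month LVEF once baseline LVEF, itself partly a measure of scar, is in the model. No correlation is given, and r could be near zero. All of this stands, and it limits the point to a question of efficiency.

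A reader might infer that the covariate would lift power from 90.3% to between 91.4% and 96.4%. The documents do not support this as the gain over the planned model. It applies a correlation that is conditional on baseline LVEF to an SD that appears not to be, and so leaves out what baseline LVEF already explains.

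A reader might also infer that viability is read centrally and blinded before randomization. Section 6.1.5 promises central blinded reading for LV function parameters and a 12-hour result for LVEF only. The scan precedes randomization; the timing and blinding of the viability reading are not stated.

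Finally, if the t-test in section 8.8 governs, a sentence in section 8.5 changes no confirmatory p-value. This also stands and belongs in the fix.

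What survives the objection is that the covariate comes from a scan made before randomization, needs no new data, and cannot bias the randomized comparison if it is fixed before unblinding.

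**Conclusion.** The point holds as an efficiency improvement. The primary model is valid, and the 60 per group, 90% power and 142 randomized are correct on their stated assumptions. A reader might infer that the trial is underpowered because of this omission; it is not, since the sample size relies on no covariate.

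Some precision may be forgone: 0% to 13% of the standard error for assumed r of 0 to 0.5, and 2% or less if r is at most 0.2. The added power at a difference of 4.5 is at most about 6 points on the reading least favourable to the planned model. It is under 1 point if 7.5 is the marginal SD and the baseline correlation is about 0.65, which the pilot data roughly suggest. The direction rests on the rationale in section 1.2; the size rests on an r that the protocol does not report.

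**What to change.** Before unblinding:

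- Add screening MRI non-viable tissue, in grams as recorded, to the primary model in section 8.5, the synopsis and the SAP, beside baseline LVEF and site. Fix this one scale in advance.
- State an exception to section 8.2 for a missing baseline covariate: site mean plus a missingness indicator, so that no patient is lost for this reason.
- Keep the present model as a sensitivity analysis.
- Confirm that the viability reading of the screening scan is blinded to treatment.
- Reconcile section 8.8 with section 8.5, so that the stage-wise p-values come from the same covariate-adjusted model. If the t-test stays confirmatory, even the adjustment for baseline LVEF is lost.

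The cost is a few sentences, one degree of freedom (a second if the indicator is needed) and a missing-baseline rule, with no new data. The drawback is that the gain is uncertain and may be small.
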